## Abstract

**Introduction:**

Patients being discharged from inpatient mental wards often describe safety risks in terms of inadequate information sharing and involvement in discharge decisions. Through stakeholder engagement, we co-designed, developed and adapted two versions of a care bundle intervention, the SAFER Mental Health care bundle for adult and youth inpatient mental health settings (SAFER-MH and SAFER-YMH, respectively), that look to address these concerns through the introduction of new or improved processes of care.

**Methods and analysis:**

Two uncontrolled before-and-after feasibility studies, where all participants will receive the intervention. We will examine the feasibility and acceptability of the SAFER-MH in inpatient mental health settings in patients aged 18 years or older who are being discharged and the feasibility and acceptability of the SAFER-YMH intervention in inpatient mental health settings in patients aged between 14 and 18 years who are being discharged. The baseline period and intervention periods are both 6 weeks. SAFER-MH will be implemented in three wards and SAFER-YMH in one or two wards, ideally across different trusts within England. We will use quantitative (eg, questionnaires, completion forms) and qualitative (eg, interviews, process evaluation) methods to assess the acceptability and feasibility of the two versions of the intervention. The findings will inform whether a main effectiveness trial is feasible and, if so, how it should be designed, and how many patients/wards should be included.

**Ethics and dissemination:**

Ethical approval was obtained from the National Health Service Cornwall and Plymouth Research Ethics Committee and Surrey Research Ethics Committee (reference: 22/SW/0096 and 22/LO/0404). Research findings will be disseminated with participating sites and shared in various ways to engage different audiences. We will present findings at international and national conferences, and publish in open-access, peer-reviewed journals.

STRENGTHS AND LIMITATIONS OF THIS STUDYThis is a best practice intervention for making discharge from acute inpatient mental health settings to the community safer and more patient centred.The study design, management and data analysis benefit from the input of experts by experience.An in-depth mixed-methods approach (qualitative and quantitative) will be used to evaluate the study and inform the feasibility and key outcomes of the main trial.A potential limitation of this study is the lack of a control condition, although an extensive baseline phase is applied for comparing data before and after introducing the intervention.

## Introduction

It is estimated that 1 in 4 adults and 1 in 10 children will be affected by mental or neurological disorders at some point in their lives.^1 2^ Mental illness has become the single largest cause of disability in England, costing the National Health Service (NHS) over £13.3 billion in 2019/2020 alone and is rising among both children and adults.^3–5^ Individuals who are admitted to inpatient mental health services are at higher risk of adverse outcomes such as shorter life expectancy; increased risk of homelessness; self-harm, violence and criminal activity; and increased likelihood of many other adverse psychosocial outcomes, including loneliness, isolation and stigma.^6–10^

Transitions into and out of acute psychiatric hospitals are risky stages in the healthcare pathway associated with patient safety issues. The absence of continuity of care is an important risk factor for patient safety incidents during transitions of care.^8^ Other patient safety risk factors may include: difficulties of medication management across the care system; delayed discharge often arising from insufficient housing, social or community care provision; and lack of information sharing between services (primarily between primary and secondary care).^6 10–14^

Multifaceted interventions have been increasingly used to improve patient safety and reduce readmissions in complex care transitions.^11 14–17^ The SAFER patient flow bundle is an exemplar multifaceted intervention, developed by NHS England/Improvement to improve discharge from acute hospitals to the community.^18^ The SAFER patient flow bundle consists of five components: (1) senior review (before midday); (2) expected discharge date and clinical criteria for discharge; (3) early assessments to improve patient flow; (4) early discharge (aiming to discharge patients before midday) and (5) a multidisciplinary review for patients with increased length of stay.^18^ Many of the individual components of the SAFER bundle are used as standard practice or best practice guidelines in policy.^19^ Preliminary evidence obtained by case studies across the country is promising as it shows that SAFER has resulted in reduced length of patient stay in different hospitals, diminished discharge delays with minimal complications and decreased readmissions or contact with primary care. Furthermore, patient and staff satisfaction have increased.^20^

Although protocols, webinars, and/or other tools have been developed to facilitate the implementation of SAFER,^20^ there is currently lack of evidence examining its appropriateness within a mental health setting. To address this gap, we conducted a series of co-design empirical studies with multiple stakeholders including patients, carers, professionals and academics.^21 22^ These led to the development of two adapted versions of the SAFER patient flow bundle tailored to mental health, one for an adult acute psychiatric hospital (SAFER-MH) and one for youth (child and adolescent) mental health services (SAFER-YMH). Now that the bundle has been developed, we aim to generate data regarding its feasibility and acceptability, which will enrich the evidence base about its future wider adoption in NHS.

The primary objectives of this research are therefore:

To examine whether the SAFER-MH and SAFER-YMH bundles are feasible and acceptable (based on standardised quantitative measures and qualitative data) to patients, carers and professionals.To identify specific principle(s) of SAFER-MH and SAFER-YMH, which need to be adapted to make it more acceptable, and increase its prospect of long-term implementation.To examine the adherence to the delivery of the intervention (measured using a purposefully designed self-report form and recruitment rates), completion rate and appropriateness of the outcome measures and recruitment strategies.To explore whether healthcare professional and patient engagement with the SAFER-MH and SAFER-YMH interventions can be increased using evidence-based behavioural science techniques.

## Methods and analysis

### Study design

This study will include two concurrent distinct studies, receiving adapted versions of the same intervention:

Phase 1: SAFER-Mental Health (MH) for adults.Phase 2: SAFER-Youth Mental Health (YMH) for children and adolescents, which includes an adaption of the original SAFER-MH for young people.

These will be uncontrolled before-and-after feasibility studies where all participants will receive the intervention. We will use quantitative (eg, questionnaires, completion forms) and qualitative (eg, interviews, process evaluation) methods to assess acceptability and feasibility.

### Intervention

The SAFER-MH is a co-designed adapted version of the SAFER patient flow bundle (NHS Improvement) intervention^18^ and will be delivered to patients as part of their normal care pathway. The intervention was adapted based on 35 stakeholder interviews and RAND consensus methods with multidisciplinary experts and professionals.^21 22^ SAFER-YMH involved a further level of co-design to ensure that the intervention is suitable for adolescent services. This involved presenting the adult version to professional and patient groups to discuss relevant changes to be made to make it more appropriate to adolescent services.

First, we aim to identify the elements of existing practice in the pilot sites before implementing the SAFER interventions, in both studies. The intervention focuses on promoting best practice guidance and has three key stages: admission, discharge and weekly tasks, and are discussed below:

#### Admission

At admission, the intervention group will complete three key tasks: (1) setting criteria for discharge and an estimated discharge day, (2) identifying early social information that will help plan for discharge and (3) introducing the patient written discharge plan. This will be structured within two documents including the admission’s social information capture document and the transition’s checklist, which will be completed at multiple times in the patient journey.

#### Weekly tasks

There are three weekly tasks that will form part of this assessment: (1) senior review of discharge readiness, (2) multidisciplinary discharge team meeting and (3) multiagency discharge team meeting.

#### Discharge

At discharge, there will be two key tasks: (1) co-producing a high-quality patient written discharge plan and (2) ensuring the patient has their copy of the patient written discharge plan.

### Participants

All patients admitted to pilot wards during the study period (14 weeks from November 2022 onwards) will receive the intervention, as it is a best practice intervention delivered as a service improvement change in care. Each individual participant who is due to be discharged from the pilot ward will then be given the option to consent (parental/guardian consent for under 16 years) whether to be a participant in the research studies by participating in the interviews and by completing relevant questionnaires. Patient participants will be adults (phase 1) or young people (phase 2) with mental illness who were admitted to an inpatient ward. Healthcare professionals who will be delivering the intervention and carers/family members of the patients (who consent to be involved) will also be involved in the interview components of the study (patient and carer interviewees can decide whether to be interviewed alone or together).

We will collect data from all consenting patients who are discharged during the baseline and intervention stages, irrespective of whether their inpatient stay began before this period. In the case of an unplanned or early discharge, we will still collect data from consenting patients who have received the intervention; if a patient is not discharged from the pilot ward (due to transfer, etc), they will be ineligible to participate.

### Eligibility criteria

#### Eligible sites

Eligible sites will be acute adult inpatient mental health wards. As this is a feasibility study, we will aim to test on a variety of wards (ie, female, male or mixed).

##### Phase 1: SAFER-MH

The eligibility criteria for individual patient participants to take part in the SAFER-MH study reflect the eligibility criteria for services. We will include adult patients aged 18–65 years, informal carers for adult patients with mental health problems aged over 18 years, healthcare professionals who are involved in delivering the intervention and informal carers of patients (for process evaluation). All patients will receive the service-level intervention but will choose to participate in the study if they feel they have the capacity and consent.

##### Phase 2: SAFER-YMH

The eligibility criteria to take part in the feasibility study reflect the eligibility criteria for services. Any young person accessing inpatient Child and Adolescent Mental Health Services (CAMHS) would be eligible to participate, as well as a parent/carer of a young person accessing inpatient CAMHS and healthcare professionals who are involved in delivering the intervention and parents/guardians of the children. All patients will receive the service-level intervention but will choose to participate in the study if they (their parents/guardians) feel they have the capacity and consent.

### Recruitment and data collection

#### Inpatient mental health ward sites

Existing networks will be used to identify eligible services (wards) for the SAFER-MH/YMH studies. The study team will meet with identified services (face-to-face or remotely) to fully explain the purposes of the studies and describe their requirements. Informed consent for services to participate will be provided by the research lead/authorised person in each service, acting as ‘guardian’ for patients in their care. This will follow agreement with each local ward team clarifying willingness to undertake the SAFER-MH/YMH interventions. Service consent to participate in the study will be formalised through written agreements. The number of services approached, declined or considered not eligible will be recorded.

##### Phase 1: SAFER-MH

We aim to recruit three pilot inpatient wards across different trusts in the northwest of England to reflect variation of NHS in England.

##### Phase 2: SAFER-YMH

We aim to recruit one or two pilot inpatient wards within one trust in the northwest of England. We do not aim to recruit additional trusts because due to funding restrictions, phase 2 must be completed by March 2023.

### Patient participants

All patients on a participating ward will receive the intervention as it is a service-level change. However, we will identify patients who are willing to participate in the study assessments (questionnaires and interviews). A ward coordinator (eg, nurse or other health professionals) working within the participating services will be asked to coordinate handing out questionnaire packs to eligible patients. Potentially eligible patients will be assigned an individual study ID and given an invitation pack close to their expected discharge. This includes an invitation letter, patient information sheet (PIS) and a consent-to-contact form.

On receipt of the invitation pack, the potential participant will complete the included documents and return these to the research practitioner on-site. Consent for researchers to contact the potential participant regarding the study will be obtained, in line with the definition outlined in Article 4 (11) of the General Data Protection Regulation(GDPR) guidance: ‘any freely given, specific, informed and unambiguous indication of the data subject’s wishes by which he or she, by a statement or by a clear affirmative action, signifies agreement to the processing of personal data relating to him or her’ (European Union, 2016). Consent to be contacted with a study recruitment pack will therefore be implied by completion and return of a completed consent-to-contact form.

### Assent for young patient participants

Assent will be sought from children/young persons’ parents/guardians, or others who are not legally empowered to give consent in phase 2.

### Carer/parent/guardian participants

A study pack will be handed to each patient at discharge; this will include a carer pack, which they can choose to pass on or discard. The pack will include details of the study, paper questionnaires and a paper consent-to-contact form for interviews, as well as an online link to assess the documents remotely. For patients who agree to be contacted for an interview, we will ask again if they would like to share the information pack and contact details with their informal carer when contacted.

### Professional participants

Staff participants will be those working directly with patient participants on participating mental health wards (ie, nurses, healthcare assistants and doctors). Staff will self-identify to be involved in interviews and questionnaires through posters on the ward and emails sent by the trust research clinician/gatekeeper containing the study information pack (PIS, invitation letter, consent-to-contact form). All staff who complete the training will be given the opportunity to complete the evaluation survey.

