### Training phase

The training will be a series of self-led short videos and self-help manuals to the pilot ward staff participating in the study. This phase will last for 2 weeks. We aim to use evaluation questionnaires following the training. Interviews in the training phase will explore whether the interventions have been fully comprehended by staff and ensure that we have enough time to solve any problems regarding the training as they arise.

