### Intervention phase

This phase will last for 6 weeks during which the wards will receive the SAFER-MH and SAFER-YMH patient flow bundle (figure 1). Data regarding the adherence of the mental health professionals to using the SAFER-MH bundle will be collected. Individual online interviews (Zoom) will be conducted with patients and carers (within 3 months after discharge) and with mental health professionals (within 1 month after the completion of the 6-week intervention phase) to assess the feasibility and acceptability of the SAFER-MH bundle. Each patient/carer will only be interviewed once; professionals may be interviewed more than once in different stages of the project. At the end of this 6-week phase, patients will be asked to complete the same study scales that were administered during the baseline and which were completed by a different pool of patient participants discharged at the time. We will also administer the three staff outcome measures after the intervention phase is complete.

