AIM, FIM, IAM	The alphas for 5-item scales were between 0.87 and 0.89. Scale refinement based on measure-specific Confirmatory Factor Analyses (CFAs) and Cronbach’s alphas using vignette data produced 4-item scales (alphas from 0.85 to 0.91). A three-factor CFA exhibited acceptable fit (Comparative fit index (CFI)=0.96, Root Mean Square Error of Approximation (RMSEA)=0.08) and high factor loadings (0.75–0.89), indicating structural validity. ANOVA showed significant main effects, indicating known-groups validity. Test–retest reliability coefficients ranged from 0.73 to 0.88.	1=completely disagree, 2=disagree, 3=neither agree nor disagree, 4=agree, 5=completely agree. Scoring instructions: scales can be created for each measure by averaging responses. Scale values range from 1 to 5. Higher scores indicate higher acceptability, appropriateness and feasibility of the intervention.

AIM, Acceptability of Intervention Measure; ANOVA, analysis of variance; CTM-4, four-item version of the Care Transitions Measure; EQUIP, Evaluating and Quantifying User and Carer Involvement in Mental Health Care Planning; FIM, Feasibility of Intervention Measure; IAM, Intervention Appropriateness Measure.

To assess professionals’ perspectives, we will use three measures: the Acceptability of Intervention Measure, Intervention Appropriateness Measure and Feasibility of Intervention Measure. Each of the three measures contains four items to assess professionals’ perspectives on a new intervention. These measures will be administered after the intervention phase only (not the baseline). Adherence to the delivery of the SAFER-MH and SAFER-YMH bundle will be measured using a purposefully designed self-report form, and recruitment rates will be recorded at each stage.

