### In-depth qualitative outcome data

A qualitative process evaluation will be conducted using semistructured interviews to provide understanding of the study delivery and its potential scale-up. All participants who complete the questionnaires will be given the opportunity to volunteer to be interviewed. We aim to interview patients and carers at baseline and intervention, whereas professionals will be interviewed at all three stages (baseline, training and intervention). All participants (including children) will be remunerated in vouchers for participation.

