### Data analysis plan

We will be following the published extension to Consolidated Standards of Reporting Trials (CONSORT)^27^ when reporting the results of this feasibility study. As this is a feasibility study, no formal sample size calculation has been conducted. Our targeted sample size (n=90, phase 1; n=40, phase 2) should be large enough to consider the practicalities of recruitment and delivering the interventions.

Descriptive statistics for intervention feasibility, acceptability and appropriateness will be presented. A chart of participant flow during the whole study will be plotted (CONSORT flow chart), which will include information on the retention/withdrawal (including timing and reasons) of wards during the evaluation. We will also present the number of health practitioners who completed the questionnaires and interviews against the number of professionals working in the wards during the evaluation, and the number of patients/carers completing the questionnaires/interviews against those discharged during the duration of the study. We will also conduct basic psychometric analyses to verify the scale structure and internal consistency of the used questionnaires. For explorative purposes, we will examine differences between the three measures completed by patients recruited during the baseline phase and the measures completed by the patients during the intervention phase. Before starting with the analyses, we will examine if the data are normally distributed. If the data are normally distributed, parametric tests will be used, otherwise non-parametric tests will be used. The significance level for all analyses will be p≤0.05. The data analyst will be blinded to the phase allocation (baseline or intervention phase).

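### Training ratings come from staff who finish the training and bundle ratings from staff still in post, so each may look more acceptable than it was

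*Protocol article*

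**What the plan says.** Two staff instruments are involved.

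- **Training evaluation survey.** Under Professional participants: "All staff who complete the training will be given the opportunity to complete the evaluation survey". The Training phase section describes two weeks of self-led videos and manuals and adds: "We aim to use evaluation questionnaires following the training". Table 1 lists the training evaluation questionnaires in the training column, so the evaluation survey is most naturally this instrument.
- **AIM, IAM and FIM.** Under Intervention phase: "We will also administer the three staff outcome measures after the intervention phase is complete". Quantitative outcomes confirms that they are given at that point and not at baseline. Table 1 sets the staff number at 45.

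The general route for staff is voluntary: "Staff will self-identify to be involved in interviews and questionnaires through posters on the ward and emails sent by the trust research clinician/gatekeeper". Interviews with professionals are planned at baseline, during training and in the intervention stage (In-depth qualitative outcome data). For reporting, the Data analysis plan sets "the number of health practitioners who completed the questionnaires and interviews against the number of professionals working in the wards during the evaluation". Withdrawal, with timing and reasons, is described there for wards.

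**The concern.** The first primary objective asks whether the bundle is feasible and acceptable to professionals, among others. The fourth asks whether engagement, including that of professionals, can be increased. Staff who never start the training, abandon it, or leave the ward while the bundle is running are informative on both questions. The text offers neither instrument to them at a time when they could answer it: the survey offer is tied to finishing, and the three scales come only at the end.

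If these staff are less favourable than the rest, the training and the bundle will each be described by their better-disposed users. AIM, IAM and FIM have no baseline or comparator, so a selected group passes straight into the reported staff result, which helps decide whether and how a main trial is run. Analysis cannot recover answers from people who were not asked.

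**Working it through.** **No figure to reproduce.** The article states that no formal sample size calculation was done, and the staff number of 45 has no derivation. The check is one of text, with an illustration of size.

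**Who can answer what, on the article's wording**

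| Staff group | Training survey | AIM, IAM, FIM | Interviews |
|---|---|---|---|
| Finished training, in post at the end | Offered | Given | Open by self-identification |
| Did not start or finish, in post at the end | No offer stated | Open; no training condition stated | Open by self-identification |
| Finished training, left during the intervention phase | Offered | No opportunity stated | Open by self-identification |
| Did not finish and left | No offer stated | No opportunity stated | Open by self-identification |

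The selection therefore differs by instrument: training completion for the survey, and remaining in post for the three scales.

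**Size for a mean score.** Let R be the mean among those measured, m the share of staff not measured, and d the amount by which the unmeasured would score lower. Then

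all-staff mean = (1 − m) × R + m × (R − d) = R − m × d,

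so the overstatement is m × d. This takes respondents as representative of those offered the instrument. Neither m nor d is in the article; the values below are assumed, on the 1 to 5 scale that Table 2 gives for AIM, IAM and FIM.

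| m | d = 0.5 | d = 1.0 | d = 1.5 |
|---|---|---|---|
| 10% | 0.05 | 0.10 | 0.15 |
| 20% | 0.10 | 0.20 | 0.30 |
| 30% | 0.15 | 0.30 | 0.45 |
| 40% | 0.20 | 0.40 | 0.60 |

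The same formula applies to the training survey, but the article gives no scale for it, so no points value can be attached.

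**Completion rate.** Take the 45 respondents of Table 1, an assumed 75 ward staff, and an assumed 20% no longer reachable when the scales are given, so 75 × 0.8 = 60 reachable:

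- against all staff: 45/75 = 60%
- against reachable staff: 45/60 = 75%

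The all-staff figure is the lower one. It does not flatter the study, but alone it cannot separate those who declined from those who were never asked.

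**The case against.** A reader might infer that only finishers may take the survey and that other staff go unheard. The text does not go so far. It promises the survey to every finisher and does not say that others are refused. Staff put themselves forward for questionnaires and interviews, and professionals are to be interviewed at all three stages; the training-stage interviews look at comprehension and at problems with the training. That stands, and it makes the gap partial. The interview route has limits, however. It depends on volunteering. The qualitative section also words the invitation as going to participants who complete the questionnaires, which fits poorly with open self-identification. Table 1 shows no interviews in the training column, although the text plans them.

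A reader might also infer that the training condition biases the bundle's scores. It does not attach to AIM, IAM and FIM: someone who drops the videos but stays may still complete them. Nor is the all-staff denominator a fault. It is the conservative choice and exposes non-response.

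The timing has reason behind it: people rate training they have received and a bundle they have used. That supports a rating at the end of the phase, but does not argue against an exit rating for leavers who have used the bundle for part of it.

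Lastly, this is a condensed article of a descriptive feasibility study, and the full protocol may hold distribution lists and exit procedures. This lowers the severity. The point rests on what the article does fix: who is offered the survey, and when the scales are given.

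**Conclusion.** The point holds in limited form. As written, training ratings come from finishers and bundle ratings from staff in post after the intervention phase, and each may look more acceptable than it was. The direction assumes that those who stop or leave are less favourable, which is plausible but not shown. The size is unknown; the range of 0.05 to 0.60 points rests wholly on assumed shares and score gaps. No figure in the article changes. Severity is minor: a cheap improvement to measures that serve two of the primary objectives.

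**What to change.** - **Professional participants and Training phase:** at the end of the two weeks, offer the training survey to all staff who were offered the training. Add an item for not started, part-completed or completed, and one for the reason for stopping.
- **Intervention phase and Quantitative outcomes:** offer AIM, IAM and FIM on exit to staff who leave during the intervention phase, and to the rest at its end as planned. Report leavers' scores separately, because their exposure is shorter.
- **Data analysis plan:** keep the all-staff denominator and add the number offered each instrument.

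The emails already sent by the trust gatekeeper can carry the wider offer. The cost is one or two extra items and a little more send-out work; headline scores and response rates may come out slightly lower.
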